### Recruitment

The primary recruitment for this study will target outpatients from Guang’anmen Hospital in Beijing, China. In addition, recruitment efforts will include posters and online advertisements providing a concise overview of the trial along with the contact information of researchers. Before enrollment, all participants will receive a comprehensive briefing on the test procedures, study’s objectives, potential adverse events, and expected benefits. During the screening phase, each participant’s eligibility for inclusion will be assessed, and they will be explicitly informed of their right to withdraw from the trial at any point. Those who choose to participate in the trial will be required to sign 2 informed consent forms: one for their records and another to be retained by the researcher.

### Randomization, Concealment, and Blinding

Random numbers will be generated using the Statistical Analysis System PROC PLAN process statement to determine the number of seeds and the segment length. Treatment assignments corresponding to running numbers 001-108 will be listed. To ensure allocation concealment, the randomization process will be managed by an independent statistician who is not involved in the study. Eligible participants will be randomly assigned to the treatment or control group in a 1:1 ratio.

Random numbers will be sealed in an opaque envelope, which will be stored in the study center. To ensure the objectivity of the research, operators and efficacy evaluators will be strictly distinguished, and efficacy evaluators and statisticians will be blinded. Only operators will have access to random numbers before treatment, and they will not be involved in the evaluation process. The selected acupoints are mainly on the lower limbs and back. The control group will also undergo acupuncture, which will ensure patient blinding. Two-stage unblinding will occur only at the end of the case collection.

### Sample Size

Referring to relevant literature [17], a formula for the superiority test is used to calculate the sample size:

where *c*=1, *n*_2_=*n*_1_; if α=.05, *u*_1_-*T*=1.64 and *u*_1_-*u*=1.28.

According to previous research [15] based on the UAS7 as the main therapeutic evaluation index, *e* is set at 9.12, *W* is set at 6, and the data are substituted into the formula to calculate *n*_1_=*n*_2_≈40. Considering a 25% dropout rate, we establish a sample size of 54 cases in each group, with a total of 108 cases.

However, it is worth noting that when conducting MRI research on the human body, the calculation of sample size does not strictly adhere to the methods used in clinical trials. Currently, there are no clear guidelines for determining sample size in fMRI studies. After an extensive review of the literature spanning the past decade, we did not find a standardized sample size calculation method for experimental studies involving brain fMRI. The previous results of the research group showed that 20 cases in each group met the statistical and practical requirements [13,14]. In this study, 40 subjects are selected for fMRI examination based on the results of previous studies and the scale of the subjects.

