### Statistical Methods

#### Primary and Secondary Outcomes

Continuous variable data following a normal distribution will be expressed using means (SDs), while those not following a normal distribution will be expressed using medians and quartiles. Categorical data will be depicted as component ratios or percentages. Group comparisons for continuous variables will be conducted using independent samples *t* tests and repeated-measures ANOVA (multiple time-point comparisons). Nonparametric data comparisons will be carried out using rank-sum tests. Categorical variables will be compared using chi-square tests or Fisher exact tests. All data analyses and graph representations will be processed using R 4.0.l software (R Project for Statistical Computing). Statistical significance will be defined as *P*<.05.

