## Results

Recruitment began on March 1, 2023. A total of 4-6 participants are expected to be enrolled per month. The recruitment is planned to be completed on March 1, 2025, and we expect to publish our results by the winter of 2025. As of November 1, 2023, we have enrolled 25 participants with CSU.

To compare all the results, including both primary and secondary outcomes, and evaluate the treatment effect, we will use R (version 4.0.1) for the analyses. ANOVA and independent samples *t* tests will be repeatedly performed for determining differences in variables between baseline and posttest in the treatment and control groups and for comparing the effects of the program between the groups. Moreover, we will determine whether there is a significant difference between the groups by judging the rejection range based on a significance level of .05. Drawing upon the outcomes of prior research, we anticipate that when comparing the primary and secondary efficacy indicators across the intervention and baseline periods, both the treatment and control groups will exhibit a downward trend in scores. However, it is expected that the decrease will be more pronounced and significant in the treatment group.

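### The sample size uses a one-sided 5% critical value, but no one-sided test is declared; under ordinary two-sided tests, 40 evaluable per arm give about 83% power rather than the implied 90%

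*Protocol article*

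**What the plan says.** In the protocol article, Sample Size, the trial is sized on UAS7: "a formula for the superiority test is used to calculate the sample size", with "if α=.05, *u*_1_-*T*=1.64 and *u*_1_-*u*=1.28". The other inputs are given as "e* is set at 9.12, *W* is set at 6", and "the data are substituted into the formula to calculate *n*_1_=*n*_2_≈40". The section then allows for losses: "Considering a 25% dropout rate, we establish a sample size of 54 cases in each group, with a total of 108 cases".

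The analysis is described in three places. Under Statistical Methods, Primary and Secondary Outcomes: "Group comparisons for continuous variables will be conducted using independent samples *t* tests and repeated-measures ANOVA (multiple time-point comparisons", and "Statistical significance will be defined as *P*<.05". Under Results: "we will determine whether there is a significant difference between the groups by judging the rejection range based on a significance level of .05". The Methods paragraph of the Abstract likewise names ANOVA and independent-samples t tests at a significance level of .05. None of these places uses the words one-sided or two-sided, and the article never writes the power as a percentage.

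**The concern.** The value 1.64 is the upper 5% point of the normal distribution, so it belongs to a one-sided 5% test; a two-sided 5% test uses 1.96. The value 1.28 is the quantile for 90% power. The size of the trial therefore rests on a one-sided test. The analysis text reads as ordinary testing for a difference, in either direction, at P<.05.

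Two things are at stake. First, if the primary test is two-sided, the power implied by the sample size is not the power of the planned analysis. Second, sidedness is part of the success criterion: a result favouring ACE with a two-sided P between .05 and .10 succeeds under a one-sided 5% test and fails under a two-sided one. A one-sided 5% test also has a 5% chance of falsely declaring ACE superior, against 2.5% in that direction for a two-sided .05 test. A trial that says it aims at definitive evidence should settle this before anyone sees unblinded data.

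**Working it through.** **Inputs**, all from Sample Size: critical value 1.64; power quantile 1.28; 9.12 and 6; allocation 1:1; dropout 25%. The formula itself is not visible in the text at hand, so reading 9.12 as the SD and 6 as the UAS7 difference is an inference. It is checked in step 2.

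**1. Reproduce the plan's figure.**

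n per arm = 2 × (1.64 + 1.28)² × 9.12² / 6² = 2 × 8.5264 × 83.1744 / 36 = 39.4, so 40.

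With dropout: 40 / (1 − 0.25) = 53.3, so 54 per arm and 108 in total. Both steps agree with the article.

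**2. Check that no other reading gives 40.** Same formula, other settings:

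| Setting | n per arm |
|---|---|
| One-sided 5%, 90% power | 40 |
| Two-sided 5%, 90% power | 49 |
| Two-sided 5%, 80% power | 37 |
| One-sided 5%, 80% power | 29 |
| One-sided 5%, 90% power, with 9.12 as difference and 6 as SD | 8 |

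Of these, only one-sided 5% with 90% power, SD 9.12 and difference 6 reproduces the stated figure.

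**3. Power at the planned 40 evaluable per arm.**

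Standard error = 9.12 × √(2/40) = 2.039. Standardised difference = 6 / 2.039 = 2.942.

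- One-sided 5%: Φ(2.942 − 1.645) = 90.3%; by the noncentral t distribution, 89.8%.
- Two-sided 5%: Φ(2.942 − 1.960) = 83.7%; by the noncentral t distribution, 82.8%.

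The type II risk is thus about 10% under the planning assumption and about 17% under a two-sided test.

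**4. How far this depends on dropout.** If all 54 per arm were analysed, the standard error would be 9.12 × √(2/54) = 1.755 and the standardised difference 3.419. Two-sided power would be Φ(3.419 − 1.960) = 92.8%, or 92.3% by the t distribution. The 83% therefore belongs to the plan's own assumption of 25% loss.

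**5. What two-sided 90% would need.** 49 evaluable per arm by the normal formula (50 by the t distribution). At 25% dropout, 49 / 0.75 = 65.3, so 66 per arm and 132 in total. This shows the scale of the gap; it is not a recommendation to enlarge the trial.

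**The case against.** The strongest reply is that the two-sided reading is drawn from silence. The sample size is expressly a superiority calculation. The Conclusions of the Abstract and the Discussion hypothesise greater improvement with active therapy, and Results expects the larger decrease in the treatment group. A one-sided t test at .05 would fit all of this, and the sample size would then be consistent as printed. The non-directional F test does not settle the matter either, because the article ties repeated-measures ANOVA to comparisons over several time points. Sidedness is also a detail that a full protocol or SAP might hold.

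Part of this stands: the two-sided reading rests on convention, and 90% is only implied by 1.28. But a directional hypothesis does not make a test one-sided, and an unqualified P<.05 for a difference between groups is ordinarily read as two-sided. Nor is this merely detail left to another document: the article prints both the one-sided quantile and the ordinary tests. An SAP that chose two-sided testing would leave the printed sample-size calculation inconsistent with it.

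It is also fair to say that 83% is above the commonly used 80%, and that power exceeds 90% if few patients are lost. That limits the consequence but does not remove the inconsistency.

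**Conclusion.** The point holds as an inconsistency between planning and analysis. The trial is sized for a one-sided 5% test with 90% power, while the analysis text describes ordinary tests at P<.05. If the primary test is two-sided, power is about 83% at the planned 40 evaluable per arm, and about 92% only if all 54 per arm are analysed. These figures assume a true difference of 6 and an SD of 9.12, both from the article, and a two-group t test.

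Three stronger inferences are not supported:

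- **That the calculation is wrong.** It reproduces exactly, including the dropout step.
- **That power is 83% whatever happens, or that 108 patients are too few.** The 83% is conditional on the full 25% loss.
- **That baseline adjustment would bring power back to 90%.** The article plans no such analysis, gives no correlation between baseline and follow-up, and does not say whether 9.12 is the SD of raw scores or of changes. At 40 per arm, if it is a raw-score SD, a correlation of about 0.45 or more would be needed; if it is a change-score SD (with equal variances), about 0.6 or less. The condition reverses, so no such claim belongs in the plan.

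**What to change.** Keep 108 patients. In Statistical Methods, state that the primary test is two-sided at .05. In Sample Size, restate the power as about 83% with 40 evaluable per arm (difference 6, SD 9.12).

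If a one-sided test is really intended, declare it in Statistical Methods before unblinding and state that the one-sided false-positive rate is 5%. The sample-size calculation can then stand.

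Do not add a statement that baseline-adjusted analysis recovers 90% power.

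The cost is about one sentence in each of the two sections, submitted as an amendment through the route the article already describes. No patients are added. Under the two-sided option, the power reported is less favourable than the one now implied.

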### Interventions

#### ACE Approach

Both the ACE and sham ACE groups will undergo acupuncture at identical acupoints in the acupuncture treatment room at Guang’anmen Hospital. To investigate the potential for ACE to extend the therapeutic duration, the control group will not receive catgut sutures. The procedure involves the insertion of a 1.0-cm catgut suture into a hypodermic needle, which is then introduced into the acupoints through the skin [18]. The angle of the hypodermic needle will be selected according to the thickness of the muscle. The hypodermic needle will be withdrawn from the skin once the patient obtains qi.

The treatment will be administered once every 2 weeks for a total of 8 weeks at the same 12 acupoints biweekly, including 4 acupoints on the dorsum, 6 acupoints on the lower limbs, 1 acupoint on the head, and 1 acupoint on the abdomen. The acupoints on the dorsum will be prone and others will be supine. These acupoints include Baihui (DU20), bilateral Xinshu (BL15), bilateral Geshu (BL17), Guanyuan (CV4), bilateral Xuehai (SP10), bilateral Zusanli (ST36), and bilateral Fengshi (GB31). The specific distribution of acupoints is provided in Table 1 and Figure 2. The precise locations of these acupoints and their Chinese pinyin names are according to acupuncture nomenclature established by the World Health Organization (WHO) [19]. The selection of these acupoints is based on a review of classical and modern literature, the neuroanatomical theory, and a consensus of acupuncture experts in Guang’anmen Hospital [20-22]. Twenty patients will be randomly selected from the ACE and sham ACE groups to undergo fMRI before and after the treatment period. For comparison, 20 healthy participants will be recruited to participate in fMRI before and after the treatment period without treatment.

The study will use sterile hypodermic needles produced by Jiangsu Zhenjiang Gaoguan Medical Equipment Co, Ltd, and 4-0’ catgut sutures produced by Jiangxi Longteng Biological Technology Co, Ltd.

**Table 1 table1:** Locations and manipulation of acupuncture points.

Acupuncture point	Location	Suggested technique
Baihui (DU20)	On the head 5 cun (traditional Chinese unit of length) superior to the anterior hairline and on the anterior median line	Subcutaneous insertion (angle of 10°-15° and depth of 10-16 mm)
Xinshu (BL15)	In the lumbar region at the same level as the inferior border of the spinous process of the fifth thoracic vertebra (T5) and 1.5 cun lateral to the posterior median line	Perpendicular insertion (depth of 20-35 mm)
Geshu (BL17)	In the lumbar region at the same level as the inferior border of the spinous process of the seventh thoracic vertebra (T7) and 1.5 cun lateral to the posterior median line	Perpendicular insertion (depth of 20-35 mm)
Guanyuan (CV4)	On the lower abdomen 3 cun inferior to the center of the umbilicus and on the anterior median line	Perpendicular insertion (angle of 90° and depth of 20-35 mm)
Xuehai (SP10)	On the lower limbs 2 cun above the medial end of the patellar base	Perpendicular insertion (angle of 90° and depth of 20-35 mm)
Zusanli (ST36)	On the lower limbs 3 cun inferior to the outer knee and on the tibial edge	Perpendicular insertion (depth of 10-15 mm)
Fengshi (GB31)	On the lower limbs 7 cun superior to the popliteal transverse line	Perpendicular insertion (depth of 10-15 mm)

**Figure 2 figure2:**
[figure not shown]
The locations of acupoints. DU: Du meridian; BL: bladder; SP: spleen; ST: stomach, GB: gall bladder; CV: conception vessel.

#### Concomitant Therapy

During the trial, only 1 H1 antihistamine can be taken. Other medicines or TCM with similar clinical efficacy, such as biological agents, H2 antihistamines, and hormones, must not be taken. If other therapies are combined, they will be recorded in the “Case Report Form (CRF).” If subjects require other treatments or concomitant care, they will need to contact the doctor in advance.

#### fMRI Examination

##### Pretest Preparation

The fMRI test will be conducted using a 3.0T Skyra (Siemens) MRI machine located at Guang’anmen Hospital, Chinese Academy of Medical Sciences. Following the completion of informed consent forms and subject checklists by the participants, the experimenter will explain the testing procedure and precautions. Prior to entering the scanning room, a thorough check will be conducted to ensure that there are no magnetic foreign objects on the participants’ bodies. Subsequently, the participants will be positioned in the supine posture on a scanning bed, and fMRI scans will be conducted under the conditions of quietude, closed eyes, and no specific cognitive activities. In the event of a rash attack, the scan will be postponed until the rash subsides for at least 12 hours.

##### Scanning Program and Parameters

A whole-brain transverse scan will be conducted in parallel with the anterior commissure-posterior commissure line and will include the cerebellum and brainstem. Resting-state functional magnetic resonance parameters will be as follows: time to repetition (TR), 2000 ms; time to echo (TE), 30 ms; flip angle (FA), 90°; layer thickness, 3.5 mm; layer spacing, 0.6 mm; 32 layers; field of view (FOV), 224×224 mm; interlayer resolution, 64×64; and scan time, 6 minutes and 46 seconds. A whole-brain 3D T1-weighted structural image will be captured through a 200-layer sagittal scan with the following parameters: layer thickness, 1.0 mm; no layer spacing; intralaminar resolution, 256×192; TR, 25300 ms; TE, 2.98 ms; FA, 7°; FOV, 256×256 mm; and scan time, 6 minutes and 3 seconds.

#### Adherence

To promote participant retention and ensure complete follow-up, the research team will initially emphasize the importance of subject compliance at the outset. The team will be in regular contact with the participants, checking on their progress once a week, providing reminders to remain engaged in treatment, and offering support throughout the treatment period. Following the completion of the full treatment regimen, participants will receive a subsidy as a token of appreciation. Participant adherence will be assessed by counting the number of treatments received, with the criterion of 80% or more of the prescribed treatments as the threshold for good adherence. The formula for calculating treatment adherence is as follows: treatment adherence = (number of treatments received by the subject / total number of treatments to be received by the subject) × 100.

### Outcomes

The study schedule is presented in Figure 3. All outcome measures explained below will be recorded from baseline until the end of follow-up.

**Figure 3 figure3:**
[figure not shown]
Schedule of trial enrollment, intervention, assessment, and follow-up. CU-Q2oL: Chronic Urticaria Quality of Life Questionnaire; DLQI: Dermatology Life Quality Index; ISI: Insomnia Severity Index; MRI: magnetic resonance imaging; SAS: Self-Rating Anxiety Scale; SDS: Self-Rating Depression Scale; UAS7: urticaria activity score over 7 days; UCT: urticaria control test.

#### Primary Outcome

The primary outcome measure for this clinical trial will be the UAS7. The UAS7 is the gold standard for CSU, evaluating 2 skin symptoms: wheals and itching. Participants will self-assess and record the severity of their symptoms on a 4-point scale. For itchiness, the scoring will be as follows: 0, no symptoms; 1, mild symptoms (occasional itching, no scratching, and no effect on life and sleep); 2, moderate symptoms (occasional itching, scratching, and life and sleep slightly disturbed, but tolerable); 3, severe symptoms (frequent itching, scratching, life and sleep disturbed, and intolerable). For wheals, the scoring will be as follows: 0, no symptoms; 1, mild symptoms (<20 in 24 h); 2, moderate symptoms (21-50 in 24 h); 3, severe symptoms (>50 in 24 h or large confluent masses). The UAS7 ranges from 0 to 42, with lower scores indicating milder skin symptoms [23].

#### Secondary Outcomes

##### Quality of Life

The quality of life measures in this clinical trial will include the Chronic Urticaria Quality of Life Questionnaire (CU-Q2oL) [24] and the Dermatology Life Quality Index (DLQI) [25]. The CU-Q2oL comprises [25] questions that assess the physical, psychosocial, and everyday impact of CSU over the past 2 weeks. Meanwhile, the DLQI comprises 10 questions that evaluate how skin problems have affected the quality of life over the past week.

##### Urticaria Control Test

The urticaria control test (UCT) measures the level of disease control among patients with CSU over the past 4 weeks. It evaluates the level of distress caused by the physical symptoms of urticaria, the impact on QoL, the effectiveness of treatment in controlling urticaria symptoms, and the overall perceived level of urticaria control. Higher scores indicate better disease control.

##### Emotion

The emotion measures in this clinical trial will include the Self-Rating Anxiety Scale (SAS), Self-Rating Depression Scale (SDS), and Insomnia Severity Index (ISI). After conversion, higher scores indicate severe emotional problems, such as depression, anxiety, and stress.

### Oversight and Monitoring

#### Data Collection and Management

The investigator will prepare original documents for each participant upon their random entry into the study. All pertinent information will be documented in the CRFs weekly and saved in a Microsoft Excel spreadsheet. The fMRI results will be archived on a CD-ROM. To ensure data integrity and quality, an internal data supervision team of researchers, led by the principal investigator, will oversee and audit clinical data. They will regularly or sporadically review the CRFs and promptly provide feedback to researchers in case of any identified issues to prevent the recurrence of similar errors or omissions. It is important to note that all participant data will be strictly confidential and not accessible to the public.

#### Quality Control

Prior to the trial’s commencement, all involved team members will undergo investigator training to acquaint themselves with the administration processes, clarify the procedures for embedding, and become familiar with fMRI [26]. Throughout the trial, each participant will be treated by the same surgeon. The head movement test involving blood oxygenation level–dependent (BOLD) images will be promptly conducted during the scanning process to ensure that head movement remains ≤1.2. If head movement exceeds 1.2, a new BOLD scan will be carried out. Following the scanning, data backup will be performed using both a removable hard disk and CD burning. There will be no changes in assignments, and the migration of individuals between groups will not be allowed. If participants discontinue treatment, the reasons for leaving the study will be recorded.

#### Safety Assessment

Adverse events that occur during treatment and follow-up, such as needle fainting, infection, subcutaneous hematoma, and subcutaneous nodules, will be recorded on the subject’s adverse event record sheet at any time. If a participant develops these adverse reactions, they will be asked to report in detail the symptoms, time of occurrence, duration, and time of abatement. Participants will be closely monitored until all indicators return to a state of complete normalcy. Serious adverse events and unintended events will be reported to the Ethics Committee of Guang’anmen Hospital and relevant authorities promptly in accordance with the regulations. The principal investigator will conduct a cumulative review of all adverse events regularly and may convene meetings with the investigators to assess the study’s risks and benefits if deemed necessary.

